**Methods:**

This multicenter study recruited Japanese patients with newly diagnosed SLE who had started glucocorticoid therapy across 15 hospitals with rheumatology services. Participants were randomly assigned in a 1:1 ratio to two groups: (1) the immediate feedback group, which receives graphical feedback on meal frequency and perceived control over eating starting from day 1, and (2) the delayed feedback group, which uses the same app without feedback for the first 14 days and begins receiving identical feedback from day 15. Participants enter data daily from day 1 to day 21 after randomization. The primary outcome is the mean number of meals on day 14 after glucocorticoid initiation. Secondary outcomes include the loss-of-control-over-eating score and a 5-item visual analog scale–based appetite score, both recorded on day 14. Between-group mean differences will be analyzed using 2-tailed *t* tests. The target sample size is 60. In an embedded observational “study within a trial,” linear mixed models will examine whether glucocorticoid dose influences appetite scores through mood and sleep changes.

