**Figure 2. F2:**
[figure not shown]
Widget interface of the Mogu!☆Log smartphone app on the LINE social networking platform. (A) Main menu widget: clockwise from the top left—Appetite, Eating Behavior Evaluation, Log Review, User Settings, Morning/Night Entry, and Actigraphy Attachment. (B) Visual analog scale (VAS) input for appetite: users slide bars to rate hunger and satiety. (**C**) VAS input for eating episodes: users rate the degree of perceived overeating and loss of control during meals. (**D**) VAS input for mood: users rate depressed mood and irritation. Values for VAS inputs are automatically calculated based on the ratio of a slider’s position (distance from the left) to the full length between labeled end points.

The immediate feedback group receives graphical feedback from day 1, whereas the delayed feedback group does not receive feedback until day 14. After that, participants receive identical real-time feedback as the intervention group. The 14-day delay was determined for the following reasons: (1) at least 7 days of data are required to capture weekly behavioral patterns [15]; (2) a feedback duration longer than 1 week is desirable to detect behavioral change [17]; and (3) the accelerometer device used in the embedded “study within a trial” (SWAT) has a battery life of approximately 21 days, determining the total study duration. Accordingly, data collection spans 21 days, comprising a 14-day intervention or control phase followed by a 7-day delayed feedback phase, ensuring both groups eventually receive feedback exposure.

To encourage adherence, participants receive Amazon e-gift cards at registration and on days 7, 14, and 21 with the amounts corresponding to their logging activities.

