#### Secondary Outcomes

Secondary outcomes include loss of control before meals, loss of control during meals, and appetite, all assessed on day 14. Loss of control is measured using a visual analog scale (VAS) comprising 2 items: before meals, “To what extent do you feel in control of your eating?” (0‐100 scale); during meals, “During meals, how much did you feel out of control?” (0‐100 scale). Appetite is measured using a validated 5-item VAS-based scale for EMA [21].

We will also examine the 21-day trajectories of loss of control (ie, before and during meals) and appetite. Given the limited evidence on how glucocorticoid affects appetite over time, these trajectories will be analyzed separately for each feedback group.

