### Statistical Analysis

For the primary outcome, meal frequency on day 14 will be compared between groups using a 2-sided Student *t* test with a 5% significance level. For sensitivity analysis, an analysis of covariance will be performed, adjusting for disease activity and glucocorticoid dose.

For the secondary outcomes, between-group comparisons of loss-of-control and appetite scores on day 14 will be conducted using the 2-tailed Student *t* test. Sensitivity analyses with analysis of covariance adjusted for disease activity and glucocorticoid dose will be conducted. Longitudinal changes over the 21-day period will be analyzed using linear mixed-effects models with random intercepts for individual participants and fixed effects for group, time, and group-by-time interactions.

For the observational SWAT, linear mixed-effects models will be used to examine associations between glucocorticoid dose and outcomes such as appetite, snacking behavior, and loss of control. Mood and sleep variables will also be analyzed using the same modeling framework to assess the effect of glucocorticoid dosage. Additionally, linear mixed-effects models will be used to assess whether mood and sleep mediate the relationship between glucocorticoid dose and appetite. All models will incorporate random intercepts for individual participants and fixed effects for group, time, and group-by-time interactions.

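### The 21-day mixed model has no term for the delayed arm's switch to feedback at day 15, so with linear time its group-by-time term cannot be read as the effect of feedback on the trajectory

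*Protocol article*

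**What the plan says.** For loss of control and appetite, the Statistical Analysis section of the protocol article first specifies day-14 t tests with covariance-adjusted sensitivity analyses. It then adds: "Longitudinal changes over the 21-day period will be analyzed using linear mixed-effects models". The stated terms are "random intercepts for individual participants and fixed effects for group, time, and group-by-time interactions". No phase, exposure or change-point term is named, and the section does not say whether time is linear or categorical.

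The Abstract says that the delayed arm "uses the same app without feedback for the first 14 days and begins receiving identical feedback from day 15". The Intervention section describes the 21 days as "comprising a 14-day intervention or control phase followed by a 7-day delayed feedback phase, ensuring both groups eventually receive feedback exposure", and Table 1 first marks delayed feedback at day 15.

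Under Secondary Outcomes, the 21-day courses of loss of control and appetite are to be examined and "these trajectories will be analyzed separately for each feedback group". The Discussion, under the advantages and challenges of graphical feedback, treats the delayed arm's change between days 14 and 21 as further evidence on what feedback does.

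**The concern.** The design has two phases and the stated model has none. For two thirds of the modelled window (14 of 21 days) the arms differ in feedback. For the remaining third (7 of 21) they receive the same thing. With linear time, one group-by-time coefficient has to fit a gap that may open up to day 14 and close afterwards. The better the delayed arm responds after day 15, the further that coefficient moves away from what happened while the arms differed.

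This matters because the model is the stated longitudinal between-group analysis of the repeated secondary outcomes, in a pilot meant to inform a full-scale trial. An intervention that works in both arms could show a flat interaction, or one that looks like a fading benefit. A reader could not tell a lost effect from a successful switch. The day 14-21 change in the delayed arm, which the Discussion wants to use, also has no term in the model.

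**Working it through.** **Inputs from the protocol article.** Days 1-21 in the model; feedback from day 1 in one arm and day 15 in the other; 60 participants allocated 1:1, taken as 30 per arm. The article gives no effect size, SD or power, so there is no stated figure to reproduce.

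**Assumptions.** Time is linear, with one score per person per day and no missing days. The benefit after k days of feedback is e(k) = δ·min(k/r, 1), and 0 for k ≤ 0, with the same build-up time of r days in both arms. The benefit of the immediate over the delayed arm on day t is then d(t) = e(t) − e(t − 14). A positive slope means a widening benefit.

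**Formula.** In a balanced random-intercept model, the group-by-time estimate is the least-squares slope of d(t) on day: Σ(t − t̄)d(t) / Σ(t − t̄)².
- Days 1-21: t̄ = 11, denominator 770.
- Days 1-14: t̄ = 7.5, denominator 227.5.

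**Example, r = 7, in units of δ.**
- Over 21 days: days 1-7 contribute (140 − 308)/7 = −24, days 8-14 contribute 0, and days 15-21 contribute 49 − 224/7 = 17. The sum is −7, so the slope is −7/770 = −0.0091.
- Over 14 days: (140 − 210)/7 + 24.5 = 14.5, so the slope is 14.5/227.5 = 0.0637.

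| Build-up r (days) | Numerator, days 1-21 | Slope, days 1-21 (δ/day) | Slope, days 1-14 (δ/day) | 21-day as share of 14-day |
|---|---|---|---|---|
| immediate | −49 | −0.064 | 0 | not defined |
| 3 | −35 | −0.045 | 0.027 | sign reversed |
| 7 | −7 | −0.009 | 0.064 | sign reversed |
| 8 | −24 + 3 + 21 = 0 | 0 | 15.75/227.5 = 0.069 | 0% |
| 10 | 10.6 | 0.014 | 0.076 | 18% |
| 14 | 23 | 0.030 | 0.071 | 42% |
| 21 | 26 | 0.034 | 0.048 | 71% |

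For the immediate effect, the mean gap over 21 days is 14/21 = 0.667δ. The fitted line therefore puts the day-14 gap at 0.667 − 3 × 0.0636 = 0.48δ, although the true gap is δ.

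**Simulation check.** The stated mixed model was fitted to simulated data (30 per arm, between- and within-person SD 1, effect 1, 60 runs per case).
- Immediate effect: the interaction averaged 0.064 per day in the direction of a shrinking benefit, and was significant that way in every run.
- 7-day build-up: it was significant in the direction of benefit in 0% of runs over 21 days, against 100% over days 1-14.

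**Illustrative power.** Assume δ = 0.5, independent within-person SD 1, 30 per arm and a two-sided 5% test.
- Standard error over 21 days: √((2/30)/770) = 0.0093. Over 14 days: √((2/30)/227.5) = 0.0171.
- 14-day build-up in both arms: 0.0357/0.0171 = 2.09 gives 55% over days 1-14; 0.0149/0.0093 = 1.61 gives 36% over days 1-21.
- Immediate effect: 0.0318/0.0093 = 3.42, so a spurious fading is declared about 93% of the time.
- Gap stays at δ from day 14 to day 21: the 21-day slope is (−10 + 49)/770 = 0.0506δ, still 71% of 0.0714δ, but power is 78% against 55%.

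**Categorical day.** Each day has its own contrast, so those through day 14 remain feedback versus none. The joint interaction test has 20 degrees of freedom and includes the seven days on which both arms receive feedback.

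**The case against.** The strongest reply is that the article never presents this interaction as the effect of feedback. It gives the direct comparison to the day-14 t tests and their covariance-adjusted versions, before the delayed arm has had any feedback. The mixed model is assigned to longitudinal change, and the stated motive is how glucocorticoids affect appetite over time. Covering all 21 days is deliberate. All of this stands, and it confines the point to a secondary analysis.

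The coding of time and the reported contrasts may also be settled in an analysis plan that is not shown. That stands for the coding, and the slope figures are conditional on linear time. It does not answer the main point: the window and the list of terms are stated, and nothing in them represents the switch.

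Three stronger readings are tempting and are not supported:
- A reader might infer that the trial's test of feedback is compromised. The day-14 analyses are untouched.
- A reader might infer that Secondary Outcomes and Statistical Analysis contradict each other. Separate models per arm would indeed contain no group term. But "these trajectories will be analyzed separately for each feedback group" can also mean group-specific curves from the joint model, so the wording is loose rather than contradictory.
- A reader might infer a far larger loss. If the immediate arm takes 14 days to build its effect and the delayed arm catches up in 7, the 21-day slope is 7/770 = 0.0091δ, 13% of the 14-day slope, and power drops from 55% to 8%. With instant catch-up it is −10/770 = −0.013δ. Nothing in the article supports a faster response in the delayed arm.

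Finally, restricting the window does not rescue the slope for an immediate effect, where the day 1-14 slope difference is 0. That is correct, and the fix has to allow for it.

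**Conclusion.** The point holds for the longitudinal secondary analysis. With linear time, the stated interaction mixes a feedback-versus-none phase with a feedback-versus-feedback phase and cannot be read as the effect of feedback on the trajectory.

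Its size depends on how fast the effect builds, which the article does not say. With equal onset in both arms it ranges from attenuation to 71% (21-day build-up), through zero at 8 days, to a reversed sign at about 7 days or less. The ratios and signs need no SD; the power figures rest on the assumed δ, SD and independence. With categorical day, only the joint test and the contrasts after day 14 are affected. The primary outcome analysis is not touched.

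**What to change.** In Statistical Analysis, choose one of two forms:
- Keep all 21 days, and add a change point at day 14/15 (level and slope) by group, or a time-varying feedback-on term. The second assumes that feedback acts alike whenever it starts, which should be stated.
- Limit the randomized longitudinal comparison to days 1-14.

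In either case, state how time is coded and report the model-based day-14 contrast, or the mean contrast over days 1-14, because a slope alone misses an immediate effect. Report days 15-21 separately, including the delayed arm's change after the switch that the Discussion wants to use. Under Secondary Outcomes, say that the separate analysis by group means group-specific curves, and that the comparison is made in the joint model.

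The cost is analysis-plan wording, and the article reports that analysis has not begun. The small downside is that limiting to days 1-14 loses some power if the gap persists after day 14 (78% to 55% under the assumptions above). The change-point form keeps all the data.

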**Figure 1. F1:**
[figure not shown]
Feedback interface of the Mogu!☆Log smartphone app on the LINE social networking platform. (**A**) Graphical feedback showing self-evaluated eating episodes. Data from the past 7 days are plotted, with days on the x-axis and time (midnight to 11 PM) on the y-axis. Label size indicates perceived overeating (larger for episodes rated as overeating), whereas label color reflects perceived loss of control (red for loss of control, green otherwise). (**B**) Graphical feedback showing the frequency of eating episodes. Data from the past 14 days are presented, with dates on the x-axis and the number of episodes on the y-axis.

Two types of feedback are provided. The first graph summarizes eating episodes over the past 7 days, indicating whether overeating or loss of control occurred (Figure 1A). The second graph presents daily meal counts over the past 14 days (Figure 1B).

Participants register the day before glucocorticoid initiation and record data from treatment days 1 to 21 (Figure 2; English translation of the Japanese text displayed in the app is provided in Multimedia Appendix 1). Appetite and mood are assessed before and 2 hours after each meal. Overeating and loss of control are recorded immediately after every eating episode, including snacks. Before starting the study, participants received instructions on voluntarily logging entries before and after meals. The app automatically sends reminders for daily reporting. Reminders for postprandial entries (2 hours after a meal) were automatically scheduled based on each participant’s self-registered typical meal times (breakfast, lunch, and dinner). Specifically, these reminders were delivered randomly within +30 or −30 minutes of 2 hours after each registered mealtime (eg, if breakfast was set at 8 AM, the reminder was sent randomly between 9:30 and 10:30 AM). In addition, for immediate postmeal entries, if a participant did not submit an entry within 60 minutes after a premeal report, an automated reminder was sent.

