### Sample Size

The target sample size is 60 participants, taking into account the rarity of newly diagnosed SLE and the constraints of study duration and funding. This pilot trial aims to obtain key data for planning a future trial, ensuring at least 30 participants to estimate parameters for outcome measures (particularly SDs), as recommended in the pilot study design literature [22].

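### The trajectory and SWAT mixed models name only a participant random intercept for several records a day over 21 days, so standard errors for group-by-time and other within-participant effects will be too small if slopes differ or nearby records correlate

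*Protocol article*

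**What the plan says.** The Statistical Analysis section of the protocol article specifies the mixed models twice. Longitudinal change over 21 days in the secondary outcomes is analysed with "linear mixed-effects models with random intercepts for individual participants and fixed effects for group, time, and group-by-time interactions". For the observational study within a trial (SWAT), which covers glucocorticoid dose, mood, sleep and mediation, it closes with "All models will incorporate random intercepts for individual participants and fixed effects for group, time, and group-by-time interactions".

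The data are dense. Under Intervention, "Appetite and mood are assessed before and 2 hours after each meal", and "Overeating and loss of control are recorded immediately after every eating episode, including snacks". The abstract adds "Participants enter data daily from day 1 to day 21 after randomization". Sample Size sets a target of 60, and the abstract gives 1:1 allocation. Table 1 records glucocorticoid as a dose per day, so dose can change within a participant; no schedule is given.

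The primary and secondary day-14 comparisons are t tests with analysis-of-covariance sensitivity analyses. They do not use these models.

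**The concern.** A model whose only random term is a participant intercept assumes that all participants within an arm share one time slope, and that any two records from a person are equally correlated whether taken on the same day, on adjacent days or three weeks apart. Records here are nested in day and in person. Dose is set by each treating physician, and the Secondary Outcomes section says there is little evidence on how glucocorticoids affect appetite over time, so the article offers nothing to support a common slope.

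If the assumption fails, the model counts within-person records as more independent evidence about slopes than they are. The trajectory comparison and any SWAT effect of a time-varying exposure would then carry intervals that are too narrow. These models carry the second study objective, and the pilot is meant to inform a larger trial.

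**Working it through.** The plan states no operating characteristic for the mixed models, so there is no figure to reproduce. The check asks what happens to a group-by-time test with no true effect.

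**Inputs from the article:** 60 participants, 1:1 (30 per arm taken); 21 days; several records a day.

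**Assumptions not in the article:** linear time; residual SD σ = 15 and intercept SD 15 on the 0-100 scale; m = 1 or 3 records a day; between-participant slope SD τ from 0 to 1 point/day; day-level SD 0 or 10; a two-sided 5% level (the article states this for the primary test only).

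**Formula for slope variation.** In balanced data the group-by-time estimate is the difference between arms in mean participant slope, so the comparison can be made per participant.

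- Spread of days about day 11: S = 2 × (1² + … + 10²) = 770.
- True variance of one participant's slope: τ² + σ²/(770m).
- Variance the random-intercept model reports: s²/(770m), where s² ≈ σ² + τ² × 770m/(21m − 1).
- Standard-error ratio r = √(reported/true); type I error = 2 × [1 − Φ(1.96r)].

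| m | τ (points/day) | True variance | s² | Reported variance | r | Type I error |
|---|---|---|---|---|---|---|
| 1 | 0 | 225/770 = 0.2922 | 225 | 0.2922 | 1.00 | 5.0% |
| 1 | 0.5 | 0.2922 + 0.25 = 0.5422 | 225 + 0.25 × 770/20 = 234.6 | 0.3047 | 0.75 | 14.2% |
| 3 | 0.25 | 225/2310 + 0.0625 = 0.1599 | 225 + 0.0625 × 2310/62 = 227.3 | 0.0984 | 0.78 | 12.4% |
| 3 | 0.5 | 0.0974 + 0.25 = 0.3474 | 225 + 0.25 × 2310/62 = 234.3 | 0.1014 | 0.54 | 29.0% |

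**Day-level effect, SD 10, independent between days, m = 3, τ = 0.** True variance = 100/770 + 225/2310 = 0.2273. s² = 225 + 3 × 20 × 100/62 = 321.8, so the reported variance is 321.8/2310 = 0.1393. Then r = 0.78 and type I error is 12.5%.

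**Simulation** (2,000 replicates per scenario, same assumptions). The last column uses a t test on participant-specific slopes, which is equivalent to a random-slope analysis here.

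| Scenario | Random intercept | Participant-clustered | Participant slopes |
|---|---|---|---|
| 3/day, random-intercept model true | 4.6% | 4.8% | 4.6% |
| 3/day, slope SD 0.25 | 12.6% | 5.2% | 5.0% |
| 3/day, slope SD 0.5 | 27.6% | 5.6% | 5.5% |
| 3/day, day effect SD 10, autocorrelation 0 | 13.2% | 5.6% | 5.4% |
| 3/day, day effect SD 10, autocorrelation 0.3 | 19.1% | 4.5% | 4.2% |
| 1/day, slope SD 0.5 | 13.6% | 5.4% | 5.4% |
| 1/day, day effect SD 10, autocorrelation 0.3 | 7.6% | 5.4% | 5.2% |

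A separate simulation of the one-record, slope SD 0.5 case gave 15%. Formula and simulation agree closely.

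**Dose.** With a dose constant within each participant, the random-intercept test rejected in 4.5% to 5.7% of runs at three records a day, in every scenario: it is a between-person contrast, which the intercept handles. With a purely illustrative within-participant dose change, the rate was 4.8% if the model was true and 6.4% to 27.0% otherwise; the upper end comes from slope SD 1 point/day. Clustered errors gave 5.0% to 6.5%. Mood and sleep effects were not simulated; they vary within person, so the same logic applies.

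**The case against.** The article says the models will incorporate random intercepts; it does not say only. A fuller analysis plan could add a residual correlation structure, degrees-of-freedom method or robust errors, and an article commonly leaves such detail out. This stands in part: absence of those details is not the point. The point is that the article lists the random and fixed parts twice and names nothing that would handle differing slopes or clustering by day.

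The inflation is also conditional, and this stands fully. No variance or correlation in the working comes from the article, and the size depends on them. At one record a day with day-level autocorrelation 0.3, type I error is only 7.6%. The article does not say whether meal-level records or daily summaries enter the models, so the three-a-day figures may not apply.

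The scope is limited too. Secondary Outcomes says trajectories are analysed separately for each group, the SWAT is exploratory, and no progression rule rests on these p values. This lowers the stakes, but Statistical Analysis still specifies group-by-time terms. The ratio r is a per-participant quantity, so by the same formula a time slope within one arm is affected equally.

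A reader might infer that every dose effect has too small a standard error, or that the trial's main comparison is compromised. Neither follows: a dose constant within participant shows no inflation, and the day-14 t tests do not use these models.

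**Conclusion.** The point holds in conditional form. The random-effects structure named for the trajectory and SWAT models is poorly matched to several records a day over 21 days. If participants differ in time slope, or nearby records correlate beyond the person mean, tests of group-by-time and of exposures that vary within a participant are anti-conservative. Under the assumed values, group-by-time error at nominal 5% is roughly two and a half to five and a half times nominal in the slope-variation scenarios, and about 13-19% with the day-level effects at three records a day. It stays at nominal if the random-intercept model is true.

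The article does not support saying that inflation is certain or giving it a single size. It supports saying that the specified structure gives no protection against it. The point concerns secondary trajectories and the SWAT, and should be dealt with before analysis, which has not begun.

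**What to change.** In the trajectory and SWAT models, add a participant-level random slope for day, or use participant-level cluster-robust standard errors with a small-sample correction (CR2). State in advance that the robust standard errors will be used if the random-slope model does not converge. Where several same-day records are analysed, also add a day-within-participant effect, or use the robust standard errors. A full set of random slopes, day effects, serial residuals and random dose slopes is heavier than 60 participants need: in the simulations, clustering by participant alone kept group-by-time error at 4.5% to 5.6% in the scenarios tabulated.

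The cost is a change to the analysis-plan wording, wider intervals and some convergence handling. Data collection is unchanged.

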## Methods

### Study Setting

This study is conducted in the rheumatology departments of 15 general or university hospitals in Japan, each comprising both outpatient and inpatient services. These hospitals were selected based on their established collaborative research relationships with the principal investigators (NK and NY) and their experience managing newly diagnosed patients with SLE.

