### Eligibility Criteria

#### Inclusion Criteria

Inclusion criteria include patients who (1) are diagnosed with SLE based on the 1997 American College of Rheumatology classification criteria [20] and (2) have initiated glucocorticoid therapy for the first time, with dosage determined at the discretion of the treating physician. There are no age restrictions; however, as rheumatology departments primarily serve adult populations, the inclusion of minors is expected to be rare. Although SLE predominantly affects women, male patients are also eligible, and sex is not used as an inclusion criterion. Participants must be able to understand Japanese because the mobile app and all study materials are available only in Japanese.

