#### Participant Timeline

Patients diagnosed with SLE and scheduled to begin glucocorticoid therapy are recruited 1 to 14 days before treatment initiation (Table 1). From days 1 to 21, all participants use the mobile app to report their mood, appetite, and eating behaviors. Participants also wear an actigraph continuously—except while bathing—to monitor their activity and sleep. Paper-based psychological and behavioral questionnaires are administered on days 1 and 21.

**Table 1. T1:** Participant timeline.

Time point in study timeline	Enrollment (day −14 to day −1)	Randomization (day 0)	Day 1 after randomization	Day 14 after randomization	Day 15 after randomization	Closeout (day 21)
Enrollment						
Eligibility assessment	✓					
Informed consent	✓					
Randomization		✓				
Intervention						
Immediate feedback			✓	✓	✓	✓
Delayed feedback					✓	✓
Assessment						
Baseline variables^a^	✓					
EMA^b^-based mood, appetite, and eating behavior^c^			✓	✓	✓	✓
Medication^d^			✓	✓	✓	✓
Actigraph-based physical activity and sleep data^e^			✓	✓	✓	✓
Paper-based questionnaire^f^			✓			✓

a Participant characteristics, including sex, birth date, age, psychiatric/psychosomatic outpatient status, height, weight, and disease activity (systemic lupus erythematosus disease activity index 2000).

b EMA: ecological momentary assessment.

c Sleep parameters, wake-up time, bedtime, mood (before sleep and before and after meals), appetite (before meals), perceived control over eating (before and after meals), and subjective assessment of meal quantity (after meals).

d Including glucocorticoids (prednisone-equivalent dose per day), psychotropic medications (hypnotics, antiepileptics, mood stabilizers, and antidepressants), hydroxychloroquine, and immunosuppressants.

e Including activity levels, nocturnal awakenings, wake after sleep onset, sleep onset latency, and sleep efficiency.

f A Three-Factor Eating Questionnaire-R18V2, Athens Insomnia Scale, Health-Related Hope Scale, and Short Grit Scale.

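### The SWAT models name a random intercept for participants but none for hospital, although dose is set by physicians in 15 hospitals; standard errors of dose effects may be somewhat too small

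*Protocol article*

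**What the plan says.** The SWAT serves the second of the two stated aims (Objectives): how glucocorticoids affect appetite through mood and sleep. Under Statistical Analysis, "linear mixed-effects models will be used to examine associations between glucocorticoid dose and outcomes such as appetite, snacking behavior, and loss of control". The same framework is then applied to mood, sleep and mediation. The paragraph closes with the structure common to these models: "All models will incorporate random intercepts for individual participants", plus fixed terms for group, time and their interaction. No hospital term, stratification by hospital or cluster-robust variance is mentioned anywhere in the article.

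Patients come from the "rheumatology departments of 15 general or university hospitals in Japan" (Study Setting). They start glucocorticoids "with dosage determined at the discretion of the treating physician" (Inclusion Criteria). On size, "The target sample size is 60 participants" (Sample Size), which is a mean of 60 / 15 = 4 per hospital. Feedback, by contrast, is allocated patient by patient by the app (Assignment of Interventions).

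**The concern.** A participant intercept accounts for repeated records of one patient. It treats two patients of the same hospital as independent. For the feedback effect this does little harm, because allocation is individual. Dose has no such protection. Physicians of one department may share prescribing habits, and their patients may share conditions that bear on eating or sleep, such as the mix of inpatients and outpatients. If dose and outcome are both correlated within hospital, the information about a between-patient dose effect is less than 60 independent patients would give, and its standard error may be understated. Some dose–appetite or dose–mood associations might then look firmer than they are. Modelling serial correlation within a patient would not help, since this correlation lies between patients.

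**Working it through.** **Inputs from the article.** 15 hospitals, 60 patients, 21 days of records, dose at the physician's discretion, participant intercept only. The sample size rests on feasibility; no effect size, SD, power or ICC is given, so there is no stated figure to reproduce.

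**Assumptions.** Dose ICC 0.3 to 0.5 and outcome ICC 0.05 to 0.2, with 0.8/0.2 as an extreme. A two-sided 5% level is assumed for the dose tests; the article states that level for the primary test only.

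**Step 1: design effect.** For a covariate correlated within clusters of size m, DEFF = 1 + (m − 1) × ICC(dose) × ICC(outcome). The standard error is too small by 1 − 1/√DEFF. With m = 4:

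| Dose / outcome ICC | DEFF | SE too small by |
|---|---|---|
| 0.3 / 0.05 | 1 + 3 × 0.015 = 1.045 | 2% |
| 0.3 / 0.1 | 1 + 3 × 0.03 = 1.09 | 4% |
| 0.5 / 0.1 | 1 + 3 × 0.05 = 1.15 | 7% |
| 0.5 / 0.2 | 1 + 3 × 0.10 = 1.30 | 12% |

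If either ICC is zero, DEFF = 1 and nothing is lost.

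**Step 2: simulated type I error when dose varies only between patients.** With a constant dose and balanced days, the participant-intercept model is equivalent to a regression on patient means. That regression was simulated with no dose effect (t test on 57 df), without and with a REML hospital intercept. Hospitals had 4 patients each, or uneven sizes 16, 9, 6, 5, 4, 3, 3, six of 2, and two of 1 (sum 60).

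| Dose / outcome ICC | Sizes | Runs | Without | With |
|---|---|---|---|---|
| 0.3 / 0.05 | equal | 6,000 | 4.9% | 4.8% |
| 0.3 / 0.05 | uneven | 6,000 | 5.9% | 5.7% |
| 0.3 / 0.1 | equal | 6,000 | 5.7% | 5.5% |
| 0.3 / 0.1 | uneven | 6,000 | 6.1% | 5.7% |
| 0.5 / 0.1 | equal | 40,000 | 6.6% | 5.7% |
| 0.5 / 0.1 | uneven | 40,000 | 7.5% | 5.9% |
| 0.5 / 0.2 | equal | 40,000 | 8.3% | 6.0% |
| 0.5 / 0.2 | uneven | 40,000 | 10.5% | 6.5% |
| 0.5 / 0 | uneven | 40,000 | 5.1% | 5.0% |

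The 95% Monte Carlo margin is about ±0.6 points at 6,000 runs and ±0.2 to 0.3 points at 40,000. The small gains in the 0.3 rows are therefore within noise. In the 0.5 rows with an outcome effect, the share of excess removed runs from (6.6 − 5.7)/(6.6 − 5.0) = 56% to (10.5 − 6.5)/(10.5 − 5.0) = 73%.

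A separate simulation with 3,000 runs gave 5.0–6.8% without and 4.7–6.2% with the term at dose ICC 0.3 and outcome ICC 0.05–0.1, and 8.0–10.0% against 6.1–6.2% at 0.5/0.2.

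**Step 3: dose that also changes within patients.** For 60 patients × 21 days, with group, time and their interaction, hospitals of 4, and half of the outcome variance between patients, the planned model's SE was compared with its true SE. Implied alpha = 2 × (1 − Φ(1.96 × ratio)).

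| Dose / outcome ICC | Constant dose: ratio, alpha | One 20% dose change at a random day: ratio, alpha |
|---|---|---|
| 0.3 / 0.05 | 0.98, 5.4% | 0.99, 5.2% |
| 0.3 / 0.1 | 0.96, 5.9% | 0.98, 5.5% |
| 0.5 / 0.1 | 0.94, 6.6% | 0.97, 5.7% |
| 0.5 / 0.2 | 0.88, 8.4% | 0.95, 6.3% |
| 0.8 / 0.2 | 0.85, 9.7% | 0.92, 7.2% |

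The 20% change is a modelling assumption only. It shows that dose variation within patients dilutes the effect.

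**Step 4: price of the term.** With no hospital effect on the outcome (0.5/0, uneven), the SD of the dose estimate rises by about 2%. In a separate run of 800 replications at a standardised slope of 0.4, power was 79.2% without and 78.9% with the term, and the largest loss in any setting was 2 points. With 800 runs each power figure carries about ±2.8 points.

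**The case against.** The strongest reply is that the sentence on random intercepts is not a full model: its list omits dose itself, as well as the mediators, so it cannot prove that a hospital term is excluded. The analysis plan is not shown and may contain one. That is fair, and nothing in the article is contradicted. What stands is that the article does state the random part common to the SWAT models and names one level only.

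Second, the ICCs are assumed. Physician discretion could mean that dose follows each patient's disease severity rather than local habit, and then the dose ICC could be low and the problem negligible. This stands, and it is why the size is given as a range.

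Third, the remedy is weak where clustering is mild. In simulation, the hospital variance was estimated as exactly zero in roughly a quarter to just under half of runs at dose ICC 0.3 and outcome ICC 0.05–0.1. In those runs the added term changes nothing. This also stands.

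Fourth, the SWAT is exploratory, within a pilot whose limited power is acknowledged (Limitations and Future Directions). That bears on severity, not on whether the point is right.

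**Conclusion.** The point holds as a conditional one of minor severity. As stated, the SWAT models treat patients of one hospital as independent while the exposure is set by hospital physicians. For a mainly between-patient dose effect, a nominal 5% test would have a type I error of about 5–7% under mild assumed clustering and 8–10% under strong clustering. The high end needs a dose ICC of about 0.5 with an outcome ICC of 0.2; uneven recruitment across hospitals makes it worse. With within-patient dose change the computed range was 5.2–7.2%.

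A reader might infer that SWAT dose findings will be false positives. The documents do not support that: they give neither ICC, and either may be near zero. A reader might also infer that the randomised feedback comparison is compromised. It is not, since allocation is by individual patient. Nor should a hospital intercept be read as a cure for confounding: it mainly repairs the standard error and does not remove confounding of dose by severity or by hospital.

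**What to change.** In the SWAT paragraph of Statistical Analysis, replace the random-effects phrase with: *random intercepts for hospital and for participants within hospital, with Kenward-Roger or Satterthwaite degrees of freedom*. The degrees-of-freedom method belongs there because about 6–6.5% type I error remained at ICCs of 0.5/0.2 with ordinary degrees of freedom; its own effect was not simulated. Keep a coded hospital identifier in the deidentified dataset. Table 1 does not list hospital among the variables, but enrolment runs through the hospitals' physicians, so it should be recoverable.

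The cost is one phrase, one software option and one coded variable, chosen before analysis begins. A random intercept adds one variance parameter, against 14 for fixed hospital effects. The downside is that, with about 4 patients per hospital, the hospital variance is imprecise and often estimated as zero, in which case the model reduces to the one now stated. Power may fall by up to about 2 points.
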